### Data analysis

In accordance with the Consolidated Standards of Reporting Trials (CONSORT) principles [49], we will report all participant flow. Demographic data will be described using summary statistics (means and standard deviations or number and percentage).

The main efficacy analysis is on an intention-to-treat basis with data from all participants. Every effort will be made to follow up all participants in both arms for assessments and the analysis will use, where appropriate, statistical techniques for handling missing data. Descriptive statistics will be used to summarise the primary outcome measures.

The secondary outcome measures will be analysed using a linear regression model, allowing for the baseline measurement of outcome, treatment assignment and NHS trust as covariates, at each assessment point separately. The coefficient of the treatment assignment is an estimate of the between-group treatment effect, and can inform potential effect sizes for a future definitive trial. Point estimates and associated 95 % confidence intervals will be reported rather than tests of statistical significance (*p* values).

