## Methods/Design

### Trial design

The Inpatient Suicide Intervention and Therapy Evaluation (INSITE) trial is designed as a single blind randomised controlled trial (RCT) with participants recruited from acute psychiatric wards from NHS trusts in the North West of England, UK. Sixty participants will be recruited and randomly allocated, using an independent source, to treatment as usual (TAU) or to TAU plus 20 sessions of Cognitive Behavioural Suicide Prevention Therapy (CBSP). TAU consists of medical and nursing care and medication as appropriate, plus multidisciplinary team management during inpatient stay. Following discharge, TAU would be variable depending on patients’ needs but typically would consist of multidisciplinary team management of community mental health team. Participants will be followed up at 6 weeks and 6 months (post intervention). The end of treatment is a fixed time and does not vary depending on treatment progress.

The project runs over three phases using a mixed-methods approach following the Medical Research Council’s (MRC’s) framework for developing complex interventions.

In phase 1, we conducted qualitative data collection from staff (*n* = 20) and patients (*n* = 20) investigating their views of inpatient care and on the implementation of CBSP, which has been used to inform the treatment and implementation protocol of the RCT. Phase 2 is the RCT evaluating CBSP reported here. Phase 3 will involve qualitative evaluation of staff and patient experiences and views of CBSP. A purposive sample of patients from both arms of the RCT will be sought to elicit a broad range of views regarding CBSP. This will include a balance of participants who have had a good outcome, those who have dropped out of the intervention and control participants. Interviews will explore participants’ and staff experiences and expectations of therapy, views on the content of CBSP and facilitators and barriers to implementation of the approach within inpatient settings. Informed consent will be obtained from all participants.

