### Recruitment and randomisation

Recruitment is over an 18-month period from May 2014 to the end of 2015. Eligible participants are identified by inpatient ward staff approached by trained research assistants or clinical studies officers from the Comprehensive Research Network (CRN). Participants deemed eligible to participate are provided with an information sheet detailing involvement in the trial and informed consent is taken 24 hours later should they wish to take part. Research assistants carry out a battery of assessments following which participants are randomly assigned to either TAU or TAU plus CBSP. Randomisation is statistician-led and pseudo-random, carried out using Sealed Envelope© Software [22] with group stratification by gender and history of self-harm. Allocation concealment is ensured as participant randomisation codes are not revealed until the participant is recruited into the trial. Participants are followed up by research assistants blinded to treatment allocation at 6 weeks and 6 months following baseline assessment. Procedures for maintaining blindness are developed for the trial, including steps and actions taken to ensure the blinding process is conducted correctly and to avoid jeopardising the blinding of the research assistant. During assessment participants are reminded by the research assistant to not disclose their treatment allocation. Blindness is monitored by the trial project coordinator who is not blinded to treatment and manages all follow-up appointments. Where blind breaches occur prior to follow-up appointments, subsequent data collection is allocated to an alternative research assistant to ensure all follow-up data is collected by blind assessors.

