### Primary outcome measures

The primary outcome is feasibility and acceptability of the intervention. Outcomes will be measured by uptake and attendance of therapy sessions during the inpatient stay and following discharge (a minimum of 10 sessions attended will be accepted as success), time spent in therapy, attrition (we anticipate a 20 % attrition rate based on similar RCTs with complex populations) and therapeutic alliance. The acceptability of the intervention and user views will be explored in phase 3 through semi-structured individual interviews with a purposive sample of participants and staff at the end of the intervention.

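### The secondary-outcome model omits gender and history of self-harm, the factors that stratify randomisation; if they predict outcome beyond baseline, its confidence intervals are conservative

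*Protocol article*

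**What the plan says.** Under Recruitment and randomisation, the protocol article describes allocation through a software service "with group stratification by gender and history of self-harm". Neither the allocation ratio nor the block size is given.

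Under Data analysis: "The secondary outcome measures will be analysed using a linear regression model", fitted at each assessment point separately, "allowing for the baseline measurement of outcome, treatment assignment and NHS trust as covariates". The treatment coefficient "can inform potential effect sizes for a future definitive trial". On reporting: "Point estimates and associated 95 % confidence intervals will be reported rather than tests of statistical significance".

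No other section adds the two stratification factors to this model. The Economic evaluation section does promise adjustment for baseline characteristics, but only for costs and QALYs. The primary outcomes (uptake, attendance, time in therapy, attrition, alliance) are to be summarised descriptively, so the regression does not touch them.

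**The concern.** Stratified allocation forces the arms to be nearly alike on gender and self-harm history. Differences between strata therefore contribute little to the true sampling error of the treatment effect. A regression without those factors does not know this. It leaves the between-stratum variation in the residual and builds the standard error from it. Where the factors are prognostic after allowing for baseline, the reported standard error exceeds the real one and the interval covers more often than its nominal 95%.

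This matters because the trial reports estimates with intervals and no tests, and those results are meant to guide a definitive trial. With 60 participants the intervals will already be wide. History of self-harm is a plausible predictor for the suicidality scales in particular, although the article offers no evidence of how strong a predictor it is.

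**Working it through.** The article states no interval width, standard deviation, effect size or power figure, so there is no figure of its own to reproduce.

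**Inputs from the article.** Sixty participants (Trial design). On attrition, Primary outcome measures says "we anticipate a 20 % attrition rate based on similar RCTs with complex populations". Expected number analysed: 60 × (1 − 0.20) = 48. Stratification factors and covariates are as set out above.

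**Assumptions not in the article.** 1:1 allocation; permuted blocks of 4 within the four gender-by-self-harm strata; half the sample of one gender; 70% with a history of self-harm; dropout at random; baseline coefficient 0.5; one trust. The partial R² of the two factors, given baseline, is varied from 0 to 0.30.

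**Degrees of freedom.** Planned model with one trust (intercept, arm, baseline): 48 − 3 = 45. With both factors added: 48 − 5 = 43.

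**Approximate formula.** Width ratio, adjusted to planned ≈ √(1 − partial R²) × t(43)/t(45), where the t quantiles are 2.017 and 2.014. For example, at 0.20: √0.80 × 1.001 ≈ 0.896.

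**Simulation.** 6,000 trials per setting. Half-widths are in units of the outcome's residual SD after baseline adjustment. The Monte Carlo error of a coverage figure is about √(0.95 × 0.05/6000) = 0.3 percentage points.

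| Partial R² | Half-width, planned | Half-width, with factors | Ratio | Formula | Coverage, planned | Coverage, with factors |
|---|---|---|---|---|---|---|
| 0 | 0.587 | 0.591 | 1.007 | 1.001 | 95.0% | 95.0% |
| 0.02 | 0.587 | 0.585 | 0.997 | 0.991 | 95.1% | 94.9% |
| 0.05 | 0.587 | 0.576 | 0.981 | 0.976 | 95.6% | 95.3% |
| 0.10 | 0.588 | 0.562 | 0.955 | 0.950 | 95.8% | 95.0% |
| 0.20 | 0.589 | 0.530 | 0.900 | 0.896 | 96.6% | 94.8% |
| 0.30 | 0.590 | 0.496 | 0.842 | 0.838 | 96.8% | 95.4% |

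Break-even lies at a partial R² of about 0.01 to 0.02. With two trusts in the model the ratios barely move (1.008 to 0.843).

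**Where the narrowing comes from.** With total residual variance held fixed, the actual SD of the planned model's estimate falls from 0.294 at a partial R² of 0 to 0.276 at 0.20. The estimate itself therefore benefits from stratification. Its reported standard error does not: at 0.20 it is about 0.589/2.014 = 0.292, and 0.292/0.276 = 1.06, about 6% too large. Adding the factors takes the actual SD only from 0.276 to 0.269, a ratio of 0.976. So of the 10% narrowing, about 2% is extra precision. The rest corrects an overstated standard error.

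**The case against.** The strongest reply is that the effect is conditional and mild. Nothing in the article shows that either factor predicts outcome once the baseline score is in the model. A baseline suicidality score already carries some of what self-harm history would tell us, and everyone enrolled has had recent suicidal thoughts or behaviour, which may narrow the contrast. The secondary outcomes also include sleep, coping style, self-concept, functioning and ward experience, where the case for self-harm history is weaker; no case is made for gender on any outcome. Up to a partial R² of 0.10, planned coverage stays between 95.0% and 95.8%. The error is on the cautious side, in a pilot that concedes insufficient power and runs no significance tests. All of this stands, and it limits the point to a worthwhile improvement.

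It could also be said that a separate analysis plan may add the factors. That does not remove the point, because the article sets out an explicit covariate list and that list does not match its own randomisation scheme.

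Three stronger readings are tempting and are not supported:

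- A reader might infer that the intervals are certainly too wide. With non-prognostic factors, adjustment makes them 0.7% wider.
- A reader might infer that the benefit of stratifying is lost. The point estimate keeps it; only the reported standard error fails to show it.
- A reader might turn the narrowing into a large gain in patients. The figure 1/0.900² = 1.23 belongs only to a partial R² of 0.20. At 0.10 it is 1/0.955² = 1.10 and at 0.05 it is 1/0.981² = 1.04. Even these describe interval width, most of which is a corrected standard error and not new information.

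Nor is there a separate result for imbalance arising through attrition. Random dropout is already inside the coverage figures, and selective dropout was not examined.

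**Conclusion.** The mismatch between the randomisation and the model is plain in the text. Its consequence is conditional: planned intervals are conservative to the extent that gender and self-harm history predict outcome beyond baseline. Over a partial R² of 0 to 0.30, adding the factors moves interval width from 0.7% wider to about 16% narrower, and planned coverage runs from about 95% to 97%. These figures rest on the assumed prognostic strength, 1:1 ratio, blocks of 4 and random 20% attrition. There is no bias in the estimate and no undercoverage. Confidence is high on the omission and its direction, and low on its size. The change should be made, but no conclusion of the trial is shown to depend on it.

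**What to change.** In Data analysis, extend the covariates of the secondary-outcome model to include gender and history of self-harm, each as recorded at randomisation, and carry the same list into the analysis plan. The article reports recruitment as ongoing, so this can be settled before analysis.

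The cost is one sentence and two degrees of freedom (45 to 43). Both variables are already needed for randomisation, so no new data are required. In the worst case examined, intervals widen by under 1%.

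Whether NHS trust belongs in the model is a separate point to reconcile: the Abstract and Trial design refer to trusts in the plural, while the Discussion says the sample came from a single trust.

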### Intervention

The intervention consists of TAU plus 20 CBSP sessions of up to 1-hour duration, over 6 months. Participants who are discharged during the treatment envelope continue their sessions in the community. TAU includes usual nursing and medical care during the inpatient stay, including medication and assessments, reviews and evaluation by the ward team. Following discharge from the ward, TAU is overseen by the appropriate care professional (e.g. care coordinator, GP, psychiatrist) and usually involves medical and multidisciplinary review and monitoring. Psychological therapies may also be offered to some participants as part of their TAU and this will be monitored.

CBSP will be delivered once or twice weekly during the participants’ inpatient stay and will continue at weekly intervals following discharge into the community. The intervention is guided by a detailed treatment protocol based on the original CBSP treatment protocol [19] but refined for use with inpatients by the project team and from data informed from pre-trial staff and patient qualitative interviews. CBSP is a recovery-based intervention, based on a detailed understanding of the individual’s experiences which aims to address and reduce the processes involved in ‘suicide schema’ activation, maintenance and elaboration using cognitive behavioural approaches. Therapy is carried out by clinical psychologists meeting the British Association of Behavioural and Cognitive Psychotherapies minimum standards for CBT practice. Treatment fidelity is maintained through adherence to a detailed treatment protocol and weekly supervision. In addition, therapy sessions are audio-recorded where permission to do so is granted. These are rated by the supervisory team, using the Cognitive Therapy Scale for Psychosis [23], to ensure therapists are adhering to CBT principles. Following the conclusion of the trial, a sample of recorded sessions will be subject to an independent fidelity check carried out by an external expert not involved in the trial.

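### The secondary-outcome regression ignores that CBSP participants share therapists; if the therapist ICC is positive, its 95% intervals will be too narrow

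*Protocol article*

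**What the plan says.** All references are to the protocol article.

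- **Model.** Data analysis specifies a linear regression for the secondary outcomes, "allowing for the baseline measurement of outcome, treatment assignment and NHS trust as covariates, at each assessment point separately". No therapist term, clustered variance or partially nested model appears there or elsewhere in the article.
- **Output.** The same section states: "Point estimates and associated 95 % confidence intervals will be reported rather than tests of statistical significance".
- **Use.** The treatment coefficient, it adds, "can inform potential effect sizes for a future definitive trial".
- **Who delivers CBSP.** Under Intervention: "Therapy is carried out by clinical psychologists meeting the British Association of Behavioural and Cognitive Psychotherapies minimum standards for CBT practice". The psychologists are plural, and only the CBSP arm sees them, for 20 sessions across six months.
- **Client and therapist pairing.** Under Therapeutic alliance and treatment fidelity, the Working Alliance Inventory is collected in client and therapist versions at session 4 and after therapy.

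The article does not give the number of therapists, their caseloads or a therapist ICC. It also does not say whether a participant keeps one therapist from ward to community.

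**The concern.** When several participants are treated by the same therapist, their outcomes can resemble each other because of that therapist's skill, style or case mix. Here this can arise in the CBSP arm only, which makes the design partially nested. The stated regression has one ordinary residual per participant. It therefore counts the CBSP participants as independent pieces of information and computes the standard error of the treatment coefficient on that basis.

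The NHS trust covariate does not repair this. Trial design speaks of several trusts, while the Discussion says the sample came from one. With one trust the term is constant and absorbs nothing. With several, it is a shift common to both arms and does not represent therapists.

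What is at stake is how honestly the uncertainty is stated. With p values set aside, the interval is the only statement of precision that a reader gets for each secondary outcome. Nothing in the plan would reveal that therapist structure had been left out.

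**Working it through.** The article gives no power, SD, ICC or derivation of the 60, so there is no figure of its own to reproduce. The check asks how far the stated interval falls short under declared assumptions.

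**Inputs from the article**
- 60 randomised (Trial design). Recruitment and randomisation says that "participants are randomly assigned to either TAU or TAU plus CBSP", without a ratio.
- Attrition: "we anticipate a 20 % attrition rate based on similar RCTs with complex populations" (Primary outcome measures).

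**Assumptions**
- 1:1 allocation, so 30 per arm; 30 × 0.80 = 24 analysed per arm.
- k = 2, 3 or 4 therapists with equal caseloads m = 24/k, and one therapist per CBSP participant.
- Therapist ICC of 0.02, 0.05 or 0.10.
- Equal total variance SD² in both arms.

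**Formulas** (n = 24)
- Design effect in the CBSP arm: DEFF = 1 + (m − 1) × ICC.
- True variance of the difference: (SD²/n) × DEFF + SD²/n. The variance assuming independence is 2 × SD²/n.
- SE ratio, true to reported: √[(DEFF + 1)/2].
- Coverage of the nominal 95% interval: 2Φ(1.96/ratio) − 1.

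**Worked extremes**
- 4 therapists, ICC 0.02: m = 6, DEFF = 1 + 5 × 0.02 = 1.10, ratio = √1.05 = 1.025, coverage 94.4%.
- 2 therapists, ICC 0.10: m = 12, DEFF = 1 + 11 × 0.10 = 2.10, ratio = √1.55 = 1.245, coverage 88.5%.

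The half-width assuming independence is 1.96 × √(2/24) = 0.566 SD. The half-width column shows what it should be.

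| ICC | Therapists | DEFF | SE ratio | Half-width (SD) | Coverage, formula | Coverage, simulated |
|---|---|---|---|---|---|---|
| 0.02 | 2 | 1.22 | 1.054 | 0.596 | 93.7% | 94.0% |
| 0.02 | 3 | 1.14 | 1.034 | 0.585 | 94.2% | 94.2% |
| 0.02 | 4 | 1.10 | 1.025 | 0.580 | 94.4% | 94.5% |
| 0.05 | 2 | 1.55 | 1.129 | 0.639 | 91.7% | 91.9% |
| 0.05 | 3 | 1.35 | 1.084 | 0.613 | 92.9% | 92.9% |
| 0.05 | 4 | 1.25 | 1.061 | 0.600 | 93.5% | 93.5% |
| 0.10 | 2 | 2.10 | 1.245 | 0.704 | 88.5% | 88.3% |
| 0.10 | 3 | 1.70 | 1.162 | 0.657 | 90.8% | 90.9% |
| 0.10 | 4 | 1.50 | 1.118 | 0.633 | 92.0% | 92.3% |

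The simulated column is a two-sample t interval at 24 per arm, 40,000 replicates per row. A separate simulation of the baseline-adjusted regression (6,000 runs) gave 88.6% (2 therapists, ICC 0.10), 93.0% (3, ICC 0.05) and 94.7% (4, ICC 0.02).

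**Sensitivity to the assumptions**
- ICC of 0: no change.
- 6 therapists, ICC 0.01: m = 4, DEFF = 1.03, ratio 1.007, so the widening is under 1%.
- No attrition (30 per arm): the ratio runs from 1.032 (4 therapists, ICC 0.02) to 1.304 (2 therapists, ICC 0.10, coverage 86.7%).

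**The case against.** The strongest reply is that both quantities driving the size, the number of therapists and the ICC, are assumed. The article describes a detailed treatment manual, weekly supervision and rated recordings, all of which aim at uniform delivery and could keep the ICC low. This stands. It means the shortfall cannot be asserted as a fact, and the 88.5% figure is a corner of the range, not an expectation.

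The second reply is that this is a pilot. The primary outcome is feasibility and acceptability, summarised descriptively. The regression serves secondary outcomes only, no significance tests are planned, and the Discussion admits insufficient power. At ICC 0.05 the half-width moves from 0.566 to between 0.600 and 0.639 SD, which changes no decision named in the article. This also stands and limits the weight of the point. It does not make the interval valid: a small trial reported through intervals alone still needs intervals that mean what they say.

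The third reply is that a condensed article may leave therapist effects to the full protocol or analysis plan, which are not shown. Such a document may indeed deal with them. The article, however, is not silent on the model: it names the terms, and the model so named assumes independence.

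Two further inferences are tempting, and the article does not support them:

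- A reader might conclude that the clustering distorts what is passed to the definitive trial. Data analysis passes on the treatment coefficient, not the interval, and ignoring therapist clustering does not bias that coefficient.
- A reader might apply the design effect to attendance and alliance and quote a reduced effective sample size. Those outcomes are only described, with no planned interval to correct, and nothing supports using the same ICC range for them.

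**Conclusion.** The point holds conditionally. As written, the regression treats participants as independent although CBSP participants share therapists and TAU participants do not. If the therapist ICC is positive, the reported 95% intervals for the secondary outcomes will be too narrow.

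The 2% to 25% range for the standard error, and coverage of about 94% down to 88.5%, rest on 1:1 allocation, 24 analysed per arm, 2 to 4 equally loaded therapists, one therapist per participant and an ICC of 0.02 to 0.10. Of these inputs, the article supplies only the 60 participants and the 20% attrition.

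A reader might infer that there are only a few therapists and that the intervals are certainly too narrow. The article says neither how many there are nor how participants are assigned to them, and the effect may be negligible. The change is worth making because it costs little, not because serious harm has been shown.

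**What to change.** 1. Keep the treating therapist of each CBSP participant as a variable in the analysis dataset. The therapist version of the alliance measure implies that this is already known. Where a participant changes therapist, record that too.
2. Report the number of therapists and their caseloads.
3. Keep the planned regression. Beside each secondary-outcome interval, give a sensitivity interval in which only the CBSP arm's share of the variance is multiplied by 1 + (m − 1) × ICC, at stated ICCs, for example 0.05 and 0.10. With equal arms and equal variances, this multiplies the standard error by √[1 + (m − 1) × ICC/2]. Fixed ICCs are preferable here because a small number of therapists cannot estimate the ICC usefully.
4. Allow for the same one-arm clustering when the results are used to size the definitive trial.

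The cost is one dataset field, a short descriptive table and one extra interval per ICC for each outcome. No further participants, visits or staff are needed. The downside is that the added intervals are somewhat wider and rest on assumed ICCs, which should be said where they are reported.
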